#### Urinary biomarkers NGAL and cell cycle arrest biomarkers

Urine will be collected at the 3 time points and analyzed for NGAL and CCA biomarkers as the product (IGFBP-7x TIMP-2) (Nephrocheck^R^ Test) as previously described in published trials [12, 21] and in accordance with the package insert guidelines. The urine values will be adjusted for albumin and for creatinine based on package insert.

### Perioperative procedures

Patients undergoing interventions on the visceral aorta will be exposed to the standard of care techniques in terms of surgery and anesthesia. For the open procedures (open juxta-, suprarenal AAA and thoracoabdominal [TAAA] repair), patients will undergo general endotracheal anesthesia (GETA) with invasive monitoring in the form of arterial line catheter placement, and central venous line (in AAA procedures) (Table 2). Endovascular techniques (TEVAR, EVAR/FEVAR/BEVAR) will be managed under general endotracheal anesthesia (GETA). Standard and invasive monitors (arterial catheter) will be placed in all, with central venous pressure and PAC catheters placed selectively based on cardiopulmonary morbidities. Given the observational nature of the study, conventional anesthetic care, fluid, pharmacologic and blood resuscitation practices will be left to the discretion of the staff anesthesiologist and surgeon. Additionally, organ protection protocols such as spinal cord and kidney protocols will all follow the standard of care at UAB (Tables 3 and 4).

**Table 2 pone.0241782.t002:** Anesthetic technique of major vascular procedures at UAB.

Anesthetic management	Open TAA	Open AAA	TEVAR	EVAR
**Anesthesia**	GETA with DLT	GETA	GETA	GETA
**Monitoring**	ASA Standard	ASA	ASA	ASA
	Rt radial A line	A line	Rt radial A line	A line
	Femoral A line	CVC	CVC	
	CVC		Spinal drain	
	TEE		SC monitoring: SSEP/MEP	
	Spinal drain			
	SC monitoring: SSEP/MEP			
**Special considerations**	LHB	Clamping/unclamping	Contrast agent	Contrast agent
	Clamping/unclamping			
**Hemodynamic goals**	**Clamping**	**Clamping**	Goal MAP> 90 mmHg following deployment of endograft	Goal MAP> 90 mmHg following deployment of endograft
	Vasodilators: NTG,Short acting beta blockers	Vasodilators: NTG, short acting beta blockers		
	**Unclamping**	**Unclamping**		
	Vasopressors: Norepi	Vaspressors: Norepi		
**Anticoagulation**	Heparin	Heparin	Heparin	Heparin
**Disposition**	ICU	ICU	ICU	Step down unit

TAA: thoracoabdominal aortic aneurysm repair; AAA: abdominal aortic aneurysm, TEVAR: thoracic endovascular aneurysm repair; GETA: general endotracheal anesthesia, DLT: double lumen tube; ASA: American Society of Anesthesiologists; Rt: right; CVC: central venous catheter; LHB: left heary bypass; MAP: mean arterial pressure; NTG: nitroglycerine; Norepi: norepinephrine; ICU: intensive care unit; SEEP: somatosensory evoked potential; MEP: motor evoked potential; TEE: transesophageal echocardiography; A-line: arterial line catheter; SC: spinal cord

**Table 3 pone.0241782.t003:** Renal protection protocol.

**Preoperative**
Discontinuation of ACEI/ARB 24 hours preoperatively unless reduced EF or heart failure
Preoperative hydration for endovascular procedures (NS 5 ml/kg/min) starting 12 hours preoperatively
**Intraoperative**
Use of high dilution of contrast agent
Intrarenal cold crystalloid (4°C), mannitol, methylprednisolone
IV mannitol 300 mg/kg post unclamping
Maintenance of MAP > 65 mmHg
**Postoperative**
Avoid nephrotoxin
Minimize contrast agents
Daily monitoring of serum creatinine/UOP
Maintenance of blood glucose 140–180 mg/dl
Maintenance of MAP > 65mmHg

ACEI: angiotensin converting enzyme inhibitors, ARB: angiotensin receptor blockers; EF: ejection fraction; IV: intravenous; MAP: mean arterial blood pressure; NS: normal saline; UOP: urine output

**Table 4 pone.0241782.t004:** Spinal cord protection protocol.

**Preoperative**
• Hold preop blood pressure medication two days prior to procedure for permissive hypertension with exception of beta blockers and clonidine, which should be continued. In patients with heart failure and/or reduced EF, discuss holding ACEI or ARB.
• All patients should be on a statin unless contraindicated
• Preoperative placement of spinal fluid drain: pop-up pressure 10 mmHg, CSF drainage < 20 ml/ hr
**Intraoperative**
• MAP > 65 mmHg with goal of MAP > 90 mmHg following deployment of endograft
• Optimization of cardiac index with vasopressors and/or inotropes
• IV naloxone drip (1 ug/kg/hr) started at beginning of case and continued for 48 hours
• Avoid long-acting narcotics (Morphine and Hydromorphone)
• Insulin drip to maintain glucose < 200 mg/dL
• Mannitol 12.5 gm prior to graft deployment and 12.5 gm after graft deployment if issues with patency of the spinal drain. Mannitol avoided if CSF drain is working well.
• Goal hemoglobin of 10 g/dL
• Mild hypothermia
**Postoperative**
• Continue insulin drip to maintain glucose < 200
• Passive rewarming in patients with mild hypothermia (>34C)
• Continue naloxone drip for 48 hours
• MAP> 90 mmHg and heart rate < 90 for 48 hours or until spinal drain removed
• Avoid arterial dilators (nitroprusside, hydralazine, milrinone) for treatment of hypertension
• CVP >10 mmHg for ventilated patients. CVP >7 mmHg for nonventilated patients
• Goal hemoglobin > 9 g/dL for first 5 days post op. Goal hemoglobin ≥10 g/dL if evidence of SCI. After 5 days if the patient is without SCI symptoms, hemoglobin goal decreased to >7 g/dL.
• CSF drainage for 24 hours at popoff of 10 mmHg. Drain clamped at 24 hours if no SCI symptoms and remains clamped for 18–24 hours with q1 hr neuro checks.
• D/C spinal drain after 72 hours if no evidence of SCI.
• Spinal drain left in place for at least 72 hours after the onset of SCI with a popoff of 10 mmHg. Spinal pressure may be lowered to alleviate symptoms.
**Rescue Maneuvers if SCI**
• If spinal drain not in place, emergent drain placement requested
• If spinal drain in place, decrease the popoff to 5 mmHg. Do not drain more than 40 mL/hr of CSF
• Transfuse to goal hemoglobin ≥ 10 g/dL
• Mannitol 12.5 grams IV over 15 minutes
• Increase goal MAP >100 mmHg unless contraindicated
• Goal cardiac index > 2.5
• Methylprednisolone 1000mg IV infusion over 30 minutes
• If not already infusing begin naloxone infusion at 1–1.5 ug/Kg/hr

MAP: mean arterial blood pressure; SC: spinal cord; SCI: spinal cord injury; CVP: central venous pressure; CSF: cerebrospinal fluid

Patients undergoing open aortic repair and F/BEVAR are typically managed in the surgical intensive care unit post-operatively.

### Surgical technique

#### Open procedures

The technique of open repair will vary somewhat with the level of disease and the surgeon performing the operation, and cannot be prescribed by this protocol given the variability in disease. However, all aortic clamp sites, renal ischemia time and methods of renal protection will be documented.

Renal protective maneuvers routinely performed by some surgeons depending on the level of disease and whether a suprarenal clamp will be placed includes ischemic preconditioning with iliac clamping prior to aortic clamping, renal flushing with cold lactated ringers containing solumedrol/mannitol, and systemic mannitol prior to aortic clamp placement [22].

#### Endovascular procedures

The endovascular techniques utilized at UAB (author [name]) depend on the clinical scenario (i.e. urgent vs. emergent repair), the devices utilized (e.g. physician modified vs. custom vs. off the shelf), the aortic pathology being treated (e.g. dissection vs. degenerative aneurysm vs. pseudoaneurysm after prior open/endovascular repair), and the level of disease (i.e. juxtarenal vs. suprarenal vs. thoracoabdominal) and the details of these various scenarios are extensive and outside of the scope of this document. These techniques have been reported in detail previously [23–26].

### Data collected

Demographic information, vital signs, laboratory values, administered medications, intravenous fluids, fluid balance, dose and type of renal contrast, cross clamp duration, mechanical ventilation data and durations will be collected at baseline and throughout the patients’ hospital stay in the study group.

The intraoperative anesthetic and postoperative intensive care management of these patients will be the responsibility of the anesthesiologist or critical care physician, respectively, and will be according to the standard of care provided for these patients.

### Outcome

The outcome is the development of AKI based on changes in serum creatinine and urine output according to Kidney Disease Improving Global Outcomes (KDIGO) criteria [27].

### Statistical analyses

The analysis plan will include comprehensive graphical and statistical descriptions of the data. Baseline demographics, biomarkers, stratified by pAKI status will be summarized using descriptive summary statistics. Continuous variables will be summarized overall and within each group with the total numbers of observations, means with 95% confidence intervals, standard deviations and ranges. The two-sample t-test will be employed to compare the mean of continuous outcome variables while the Wilcoxon rank-sum test will be used for study outcomes that do not meet the normality assumption after performing appropriate data transformations. Categorical variables will be summarized overall and within each group with the total numbers of observations and percentages with exact 95% confidence intervals. To assess the accuracy and concordance of each marker with the pAKI status, we will calculate sensitivity and specificity. We will evaluate concordance (sensitivity and specificity) between pAKI status and SWE, uCCA, uNGAL alone and in combination. The BSI accuracy in predicting pAKI status will be evaluated in this study. To investigate the prognostic utility of bio-sonographic index for prediction of pAKI status, we will compare the sensitivity and specificity, using the 10% change from baseline to any of the 6 and 24 hour postoperative values alone as well as combined score (range: 0–3). Receiver operating curve (ROC) will be constructed for comparison between individual and combined components of SWE, uCCA, and uNGAL, and the differences in areas under the curve (AUC) will be assessed using a critical “z” ratio proposed by Hanley and McNeil. Intra-subject variability will be examined by comparing difference of individual readings from the median YM for each subject. The diagnostic performance of SWE and combination of each for distinguishing normal renal parenchyma from renal parenchyma affected by AKI will be assessed using a univariate logistic regression model to construct receiver operating characteristic (ROC) curves. ROC analyses will be performed to determine a cut-off point of SWE that would correctly classify the maximum number of participants based on sensitivity and specificity values. Wald asymptotic 95% confidence limits will be presented for sensitivity and specificity values. Percentile method 95% confidence intervals for ROC curves will be generated using the pROC package in R version 3.0.2 (Vienna, Austria) [28, 29]. Comparisons of area under the curves will be performed by use of a contrast matrix to take differences of the area under the empirical ROC curves. Pearson correlation coefficients will be used to assess the strength of association between continuous exposure variables. Stratified analysis of the control and AKI groups will be performed to evaluate for potential significant confounders of SWE values. SAS version 9.4 (Cary, NC) will be used for all other non-ROC related statistical analysis. Two-tailed p values of less than 0.05 will be deemed statistically significant.

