**Discussion:**

We hypothesize that the BSI will be a sensitive index of early structural abnormalities that precede and predict the occurrence of AKI as defined by KDIGO in complex vascular surgery.

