## Introduction

Postoperative acute kidney injury (pAKI) is a common complication of aortic aneurysm repair occurring in approximately 40% of patients [1–4]. Even in milder forms, pAKI has been associated with progression to chronic kidney disease (CKD), high mortality, morbidity and health care expense. Although patients may recover renal function after acute injury, there is no curative treatment available [5].

A major impediment to the provision of early and effective treatment for pAKI is the inherent delay in diagnosis due to limitations of available markers of kidney function, which are neither sensitive nor specific to the site, laterality, extent, etiology or reversibility of the injury [6–8]. Additionally, current novel biomarkers of renal injury such as neutrophil gelatinase-associated lipocalin (NGAL) suffer from the limitations of being non-specific to the etiology of renal injury, being heavily affected by preoperative kidney function status [9], lack of current consensus on cut off values [10], and the inability to use as therapeutic targets. As such, the diagnosis of pAKI continues to be delayed with consequential delay in initiation of effective and timely therapy and improved outcomes.

Whereas G1 cell cycle arrest (CCA) biomarkers (urinary insulin growth factor binding protein-7, IGFBP-7 and inhibitor of tissue metalloproteinase-2, TIMP-2) have been recently validated as markers of renal stress that predict the occurrence of pAKI [11, 12], they are affected by preoperative disease comorbidities, do not inform on non-tubular nephron pathology, and have been used in such a way that therapy based on their use has been confined to the postoperative period after the occurrence of the injury [13].

Shear wave elastography (SWE) has evolved as an ultrasound tool capable of measuring and quantifying tissue stiffness in response to stress. Tissue stress is applied by emitted U/S beam that generate shear waves, the velocity of propagation of which is measured as a surrogate of deformation (or elastance or stiffness) using Young’s Elastic Modulus (YM). The stiffer the tissue, the faster the propagation velocity [14]. Shear wave elastography has been recently used to assess renal tissue stiffness in patients with mild forms of chronic kidney disease (CKD) [15–17]. We hypothesize that detection of renal cortical stiffness may add to the diagnostic value of currently used renal biomarkers.

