### Procedures

The bio-sonographic index (BSI) will be performed on the study patients at baseline- during their preoperative visit, and at 6 hours and at 24 hours after the procedure. The BSI will be composed of SWE, urinary cell cycle arrest (uCCA) and urinary NGAL (uNGAL). Abnormal BSI will be diagnosed as an increase of at least 10% from baseline to any of the 6 and 24 hour time points. Based on an estimated incidence of pAKI of 40% in this population, a probability of abnormal BSI will be estimated as follows (Table 1).

**Table 1 pone.0241782.t001:** The BSI criteria.

AKI	combination	SWE (YM)	uCCA	uNGAL	Patients	AKI %
Y	Abnormal	≥10% = 1, < 10% = 0	≥10% = 1 < 10% = 0	≥10% = 1 < 10% = 0	40%	90%
N	Normal	SWE <10% = 0	< 10% = 0	< 10% = 0	60%	30%

* Values are in reference to a change from baseline to any of time points 2, and 3.

AKI (Y/N) = YM based on SWE & urine biomarkers

AKI: acute kidney injury; SWE: shear wave elastography; YM; Yong Elastic Module; uCCA: urinary cell cycle arrest; uNGAL, urinary neutrophil gelatinase-associated lipocalin; Y: yes; N: no; BSI: biosonographic index; BSI score is the sum of SWE, Biomarker, and NGAL. It is abnormal if ≥ 1. Total score can range from 0 to 3.

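### No analysis named in the plan isolates what SWE adds to uCCA and uNGAL, and a BSI that beats one urinary marker does not show that SWE adds

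*Protocol article*

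**What the plan says.** All references are to the protocol article. It carries two hypotheses.

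- The Introduction, at the end of its paragraph on elastography, states: "We hypothesize that detection of renal cortical stiffness may add to the diagnostic value of currently used renal biomarkers". This is a conditional claim about SWE, given the markers already in use.
- The Abstract (Discussion) states: "We hypothesize that the BSI will be a sensitive index of early structural abnormalities that precede and predict the occurrence of AKI". This concerns prediction by the whole index.

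The footnote to Table 1 (Procedures) defines the index as an unweighted total: "BSI score is the sum of SWE, Biomarker, and NGAL". Each item is 0 or 1 according to a 10% rise from baseline.

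Statistical analyses names these comparisons:

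- Sensitivity and specificity: "We will evaluate concordance (sensitivity and specificity) between pAKI status and SWE, uCCA, uNGAL alone and in combination". A later sentence compares them "using the 10% change from baseline to any of the 6 and 24 hour postoperative values alone as well as combined score (range: 0–3").
- AUC: "Receiver operating curve (ROC) will be constructed for comparison between individual and combined components of SWE, uCCA, and uNGAL", where "the differences in areas under the curve (AUC) will be assessed using a critical “z” ratio proposed by Hanley and McNeil".
- Regression: performance of SWE and its combinations "will be assessed using a univariate logistic regression model to construct receiver operating characteristic (ROC) curves".

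The combinations are not listed. The uCCA+uNGAL pair is neither named nor excluded, and no model with and without SWE is named.

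**The concern.** The hypothesis on SWE corresponds to the null that, once uCCA and uNGAL are known, SWE carries no further information about pAKI. Comparing the three-item score with a single marker tests something else: whether the total ranks patients better than one of its parts. That null is false whenever two urinary markers together beat one, even if SWE is noise.

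A significant result for BSI over uCCA, or BSI over uNGAL, could therefore be taken as support for elastography when the second urinary marker produced it. SWE is the new component and the laborious one: both kidneys, three time points, two operators and repeated measurements. The closing paragraph of the Discussion says the data will feed a later randomised trial, so whether SWE earns its place in the index is worth a direct answer.

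**Working it through.** **The plan's own figure.** Sample size calculation claims at least 90% power for Fisher's exact test, 69% v 30%, groups of 32 and 48, two-sided 5%. Exact enumeration gives 92.8%, so the figure reproduces. It concerns pAKI rates by BSI status. No power is stated for any AUC difference.

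**Inputs.** From the document: 32 pAKI and 48 non-pAKI patients, a 10% cut per marker, score 0–3, two-sided 5%. Assumed, because the document gives no marker AUCs or correlations: normally distributed changes, with the cut at 0, 0.5 or 1 SD of the non-pAKI distribution. A shift of d SD corresponds to AUC = Φ(d/√2), so 0.75 SD gives Φ(0.530) = 0.70 and 1 SD gives Φ(0.707) = 0.76.

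**Why noise in SWE does not stop the score from winning.** Take independent urinary markers shifted 1 SD, cut at 0.5 SD, and SWE pure noise.

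- Positive rates: 1 − Φ(−0.5) = 0.6915 in pAKI and 1 − Φ(0.5) = 0.3085 in non-pAKI. SWE is positive in 0.3085 of both groups.
- One dichotomised urinary marker: AUC = (1 + 0.6915 − 0.3085)/2 = 0.69.
- uCCA+uNGAL score: P(0, 1, 2) = (0.0952, 0.4266, 0.4782) in pAKI and the reverse in non-pAKI. P(higher) = 0.4266×0.4782 + 0.4782×0.9048 = 0.6367. P(tie) = 2×0.0952×0.4782 + 0.4266² = 0.2731. AUC = 0.6367 + 0.2731/2 = 0.77.
- 0–3 score: the two-marker difference D takes the values 2, 1, 0, −1 with probabilities 0.2287, 0.4080, 0.2731, 0.0812. The SWE difference is +1 or −1 with probability 0.3085×0.6915 = 0.2133 each. AUC = 0.2287 + 0.4080×(0.7867 + 0.1067) + 0.2731×0.5 + 0.0812×0.1067 = 0.74.

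Adding SWE lowers the score's AUC from 0.77 to 0.74, yet the score still exceeds the single marker's 0.69.

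**Rejection rates with SWE pure noise.** Paired AUC test (DeLong), z > 1.96 in favour of the score; urinary shifts 0.75–1 SD, equal; correlation 0–0.3:

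- score beats a given dichotomised urinary marker: about 9–29%
- score beats at least one of the two: 18–52%
- 1-df likelihood-ratio test of SWE given both urinary markers (threshold 3.841): 4–7%

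With unequal urinary markers (AUC 0.80 and 0.65), the score beats the weaker in 54–57% and the stronger in only 0–2%.

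**A second grid.** Urinary AUC 0.75 each, correlation 0.3; false-positive rates 15%, 30% and 50%; 2,000 runs per cell:

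| SWE | Score v one urinary marker | Score v uCCA+uNGAL score | Nested likelihood-ratio test |
|---|---|---|---|
| AUC 0.50 (noise) | 11–19% | 0.1–0.2% | 5–6% |
| AUC 0.66, nothing beyond the urinary markers | 30–35% | 1–2% | 5–6% |
| AUC 0.65, adds | 45–52% | 8–11% | 52–55% |
| AUC 0.70, adds | 63–70% | 20–25% | 78% |
| AUC 0.75, adds | 78–84% | 40–47% | 93–94% |

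The Hanley–McNeil test, which the plan names, rejects less often: 6–13% in the first row and 22–27% in the second for the single-marker contrast.

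**If SWE does add.** SWE shift 0.75–1 SD, urinary shifts 0.75 SD, correlation 0 or 0.3:

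- score v uCCA+uNGAL score: about 13–54%
- nested likelihood-ratio test with continuous changes: 41–97%
- score v one dichotomised urinary marker: 46–82%

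**Share due to dichotomising.** At an SWE shift of 0.75 SD and correlation 0, the likelihood-ratio test has 80–82% power with continuous markers and 61–65% with 10% indicators. So the gap is not all due to the AUC contrast.

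**The case against.** The main hypothesis is that the whole BSI predicts AKI, and the named accuracy analyses address it. The added-value statement is one tentative sentence in the Introduction. The document never says that beating one marker will prove that SWE adds. Its wording on combinations leaves room for uCCA+uNGAL against all three. The study calls itself exploratory, and an article may leave the list of models to a fuller plan. All of this stands, and it limits the point to a mismatch between a secondary hypothesis and the analyses named for it.

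Two further limits stand. The 9–29% are not type I errors, because the null being tested really is false in those settings; the fault would lie in the inference drawn. And the rates depend on assumed markers, falling to 0–2% against a clearly stronger urinary marker.

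A reader might also infer that comparing the score with a single marker generally has low power when SWE does add. That is not supported. Against a dichotomised urinary marker the power was 46–82%, beside 41–97% for the likelihood-ratio test. Across other assumed AUCs it ran from 15% to 95%, depending on the comparator. The trouble with that contrast is what a rejection means, not how often it occurs.

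Reading the pair into the wording does not fully answer the concern, because the three- against two-marker score contrast is the weak one.

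**Conclusion.** The concern holds in a limited form. The Introduction hypothesises that SWE adds to current biomarkers, and no analysis named under Statistical analyses isolates SWE given uCCA and uNGAL. A win over one urinary marker cannot fill that gap: with SWE as noise and two equally good urinary markers it occurs in about 9–29% of simulated trials. If the uCCA+uNGAL pair is read into the plan, the score contrast has about 13–54% power where a nested likelihood-ratio test has 41–97%, with part of the difference due to the 10% cut.

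These sizes rest on normal markers, assumed shifts of 0.75–1 SD, correlation 0–0.3, a 32/48 split and DeLong tests. The logical point does not depend on them. The document does not support the stronger statements that the plan excludes pairs, or that its main hypothesis goes untested. This is a low-cost improvement to the analysis text and does not invalidate the study.

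**What to change.** In Statistical analyses, name one test of added value: a logistic model for pAKI with continuous log change in uCCA and uNGAL, fitted with and without continuous log change in SWE, and a 1-df likelihood-ratio test for SWE. Define change once for all three markers. The larger of the 6- and 24-hour changes would match the score's rule, since a 10% rise at either time is the same as the larger rise reaching 10%. Report the AUC with and without SWE, and the difference with its interval, optimism-corrected, as description.

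Keep the sensitivity, specificity and ROC analyses of the BSI for the main hypothesis. List the combinations to be compared, and state that BSI against a single marker is not evidence that SWE adds.

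The cost is some wording and one extra model on data already collected. The model has three predictors on about 32 expected events (40% of 80), which is modest but leaves estimates imprecise. Its power is itself only about 41% in the least favourable setting examined, so a non-significant result should be reported with its interval and not read as showing that SWE adds nothing.

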### Sample size calculation

Based on our prior experience and literature search of a 40% incidence of pAKI in this population encompassing both open and endovascular approaches of descending aortic aneurysm repairs [1, 18, 19], we expect 40% patients to develop pAKI and 60% of patients to not develop pAKI. We project that more than 70% of patients with a positive BSI to develop pAKI, while only 30% of those with a negative BSI to actually develop pAKI. From this assumption, if we recruit 80 patients to the study, we will have 32 patients expected to have pAKI (positive BSI) and 48 patients expected not to have pAKI (negative BSI). Using Fisher’s Exact Test with a 5% two-sided significance level, we will have minimum 90% power to detect the difference between 69% pAKI in patient group who will eventually develop pAKI (positive BSI) and 30% pAKI in patients who will not eventually develop pAKI (negative BSI), when sample sizes are 32 and 48, respectively. In addition, we will recruit 15 healthy group of participants to explore the feasibility of the SWE protocol, and to establish reference values on a sample of our population in terms of renal cortical stiffness, and renal parenchymal and vascular indices.

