### Participants

A total of 80 patients for the ‘study group’ will be enrolled. Each patient will serve as his/her own control by studying the change in BSI from preoperative values to 6 and 24 hr after the procedure. A total of 15 normal healthy volunteers will be enrolled as a ‘feasibility group’ to test the feasibility of the SWE protocol.

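### The SWE cut-off is optimised on the study's own ROC curve and then given Wald limits as if fixed in advance, so its reported accuracy is somewhat too high and its intervals too narrow

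*Protocol article*

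**What the plan says.** All of this is in the protocol article.

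- **Choice of cut-off (Statistical analyses).** "ROC analyses will be performed to determine a cut-off point of SWE that would correctly classify the maximum number of participants". The sentence closes by tying this choice to both accuracy measures, sensitivity and specificity.
- **Uncertainty (next sentence).** "Wald asymptotic 95% confidence limits will be presented for sensitivity and specificity values".
- **Other intervals (the sentence after that).** "Percentile method 95% confidence intervals for ROC curves will be generated using the pROC package". These are for the curves and are not described as a correction for choosing a cut-off.
- **Data (Participants; Sample size calculation).** "A total of 80 patients for the ‘study group’ will be enrolled", and "we expect 40% patients to develop pAKI and 60% of patients to not develop pAKI", which is 32 and 48 of 80. The 15 healthy volunteers have no intervention and no AKI outcome.
- **A separate, fixed rule (Procedures, Table 1).** Each BSI component scores 1 for a rise of at least 10% from baseline. This threshold is set before the data are seen.

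**The concern.** A cut-off picked because it classifies these patients best partly fits their chance pattern, so sensitivity and specificity read off at that point are too favourable on average. The Wald formula treats the cut-off as a constant. It allows for binomial error at a given point, but not for the search that found the point or for the upward shift that the search causes. At stake is the published accuracy of SWE as a single marker, which readers will compare with the biomarkers and with the combined score.

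A secondary point is that the selection criterion is not stated clearly. Taken literally, maximising the number classified correctly weights specificity by 60% and sensitivity by 40% at the expected prevalence. Youden's index weights them equally. The two rules can give quite different cut-offs.

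**Working it through.** **The plan's own figure.** The article gives no accuracy figure for the SWE cut-off. Its only design figure is power of at least 90% for 69% against 30% with 32 and 48 patients (Fisher's exact test, 5% two-sided). Exact enumeration gives 92.8%, which agrees. Nothing below depends on it.

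**Inputs.** AKI 0.40 × 80 = 32, non-AKI 48 (Sample size calculation). The true SWE AUC is not in the document. It is an assumption, varied from 0.60 to 0.90.

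**Model (assumed).** SWE is N(0,1) without AKI and N(d,1) with AKI, where d = √2 × Φ⁻¹(AUC). In each simulated study the cut-off was chosen from the 80 patients. The apparent value at that cut-off was compared with its true value: sensitivity 1 − Φ(c − d), specificity Φ(c). Coverage is the share of studies in which the Wald interval p ± 1.96√(p(1 − p)/n) contains the true value at the chosen cut-off.

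**Maximum-accuracy rule** (20,000 replicates per AUC, ties broken at random; apparent / true):

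| AUC | Accuracy | Sensitivity | Specificity | Coverage, sens. | Coverage, spec. |
|---|---|---|---|---|---|
| 0.60 | 0.65 / 0.60 | 0.31 / 0.25 | 0.88 / 0.83 | 92% | 71% |
| 0.70 | 0.70 / 0.65 | 0.50 / 0.44 | 0.84 / 0.79 | 90% | 80% |
| 0.80 | 0.77 / 0.72 | 0.65 / 0.60 | 0.85 / 0.81 | 88% | 83% |
| 0.90 | 0.85 / 0.81 | 0.79 / 0.75 | 0.89 / 0.86 | 85% | 82% |

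Accuracy is overstated by 3.6 to 5.1 points. Several cut-offs often tie for best, and the article gives no tie rule. Taking always the lowest or always the highest tied cut-off widens the coverage range to about 84–93% for sensitivity and 66–84% for specificity. Part of the low specificity coverage at weak AUCs arises because Wald limits have zero width when the estimate is 100%.

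**Youden rule.** At AUC 0.70, sensitivity is 0.69 / 0.63, specificity 0.68 / 0.64 and J 0.37 / 0.27. Under the literal rule J is 0.34 / 0.24. Over AUC 0.60–0.90, Youden coverage is about 80–85% for sensitivity and 85–89% for specificity.

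**Cut-off fixed in advance (at d/2).** Apparent and true values agree to within 0.2 points, and Wald coverage is about 92–95%. The bias therefore comes from the selection.

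**What the criterion changes.** Population accuracy is 0.4[1 − Φ(c − d)] + 0.6Φ(c), which is greatest at t = d/2 + ln(0.6/0.4)/d. At AUC 0.70, d = 0.742 and t = 0.371 + 0.405/0.742 = 0.917. Sensitivity is then 1 − Φ(0.176) = 0.43 and specificity Φ(0.917) = 0.82. At the Youden point both are Φ(0.371) = 0.645.

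| AUC | Max-accuracy sens. / spec. | Youden, both | Sensitivity given up |
|---|---|---|---|
| 0.70 | 0.43 / 0.82 | 0.645 | 21 points |
| 0.80 | 0.60 / 0.83 | 0.72 | 12 points |
| 0.90 | 0.75 / 0.87 | 0.82 | 7 points |

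**The case against.** **An unseen analysis plan may add internal validation.** This is fair: an article may leave such detail out, and the missing correction is not the point here. What the article does fix is a data-driven cut-off and Wald limits. A later plan would have to replace that interval method, not merely add to it.

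**The Wald sentence is general.** It could be meant for the fixed 10% rule, where it raises no selection problem. But it directly follows the cut-off sentence and is not restricted, so as written it covers both.

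**The criterion may be Youden.** The cut-off sentence ends by referring to sensitivity and specificity, which permits that reading. If so, the sensitivity trade-off falls away, but the optimism does not.

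**The effect is modest.** The Wald half-width is 1.96√(0.6 × 0.4/32) = 17 points for a sensitivity of 0.6 and 1.96√(0.8 × 0.2/48) = 11 points for a specificity of 0.8. Both exceed the bias. The study calls itself exploratory and defers validation. This limits the weight of the point, but later validation does not correct the estimates and limits published from this study.

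A reader might also draw three stronger conclusions, none of which the article supports:

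- *That the rule contradicts the study's aim.* The hypothesis "We hypothesize that the BSI will be a sensitive index of early structural abnormalities" concerns the BSI, which does not use this cut-off. The main Discussion credits adding imaging with better specificity of the biomarkers.
- *That this cut-off goes into the next trial.* The main Discussion speaks of validating the 10% change, the index and the study's data. It does not mention the ROC-derived SWE cut-off.
- *That the headline BSI accuracy is inflated by this.* It rests on the prespecified 10% rule.

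**Conclusion.** The point holds for the derived SWE cut-off. Following the stated analysis gives accuracy about 4 to 5 points too high under the literal rule, with a similar bias under Youden, and 95% limits that cover less often than claimed. The shortfall is largest for specificity under maximum accuracy and for sensitivity under Youden. The sizes rest on an equal-variance binormal marker, a 32/48 split and an assumed AUC. The direction is the same from 0.60 to 0.90. That selection and evaluation share the same patients is inferred from the article describing no other outcome data, and the inference is firm.

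The sensitivity trade-off supports only a request to state the criterion. It is conditional on maximum accuracy being meant, and it shrinks as the AUC rises. Overall this is a secondary but real flaw that is worth correcting.

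**What to change.** 1. For the derived SWE cut-off, replace the Wald limits with a bootstrap that repeats the cut-off selection, and any combined logistic model fit, in every resample.
2. Report optimism-corrected sensitivity and specificity with limits from that bootstrap, centred on the corrected estimates. Plain percentile limits of re-optimised apparent values would carry the same optimism.
3. Label the cut-off as derived, not validated.
4. State the selection criterion: Youden's index, the highest specificity at a stated minimum sensitivity, or maximum accuracy with its prevalence weighting acknowledged. Add a rule for ties.
5. Keep Wald limits, or exact ones, for the fixed 10% rule.

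This needs no new patients or data and only a small addition to the R work already planned. The price is slightly more analysis and less favourable reported accuracy.
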